### Intervention

The UCSD RELINK intervention involves a Health Coaching psychoeducational program and Service Navigation support. The Health Coaching curriculum will be available in a printed workbook and on the study website which will host a digital workbook as well as videos that offer participants an audio-visual version of the workbook to facilitate learning for low literacy audiences. Table 1 summarizes the Health Coaching modules which are founded on cognitive-behavioral theories suggesting that emotions and behaviors influence our evaluation of the social and physical contexts in which we live (Beck & Beck, 1995). Individuals who have negative beliefs or skills deficits, such as poor emotional regulation, poor problem solving/self-advocacy skills, may have negative emotions and potentially, engage in health-damaging behaviors. Alternatively, persons with greater social and cognitive skills, such as goal setting, self-insight, executive functioning, may exhibit greater engagement in health-supporting behaviors. The Health Coaching program is designed to support participants’ acquisition self-insight and promote self-efficacy across a range of health and healthcare utilization domains (Bath, 2008; Berghuis, 2018; Brun & Rapp, 2001; Epstein & Street, 2011; Levenson & Willis, 2019; Miller & Rollnick, 2012; Wachtel & McCold, 2001). Health Coaching module-completion certificates and a final diploma are provided to reinforce learning and goal attainment.

**Table 1 Tab1:** UCSD RELINK Health literacy curriculum to address disparities in healthcare access. (Available via a printed workbook and electronically via the study website as an electronic document or videos)

Module type	Module titles	Module learning objectives
**Core modules** *All required*	1. Program Orientation 2. Vision & Values 3. Goal Setting & Problem Solving 4. Stimulus Control 5. Navigating Health Services & Insurance 6. Communicate Effectively with Providers 7. Preventive Care (vaccines) 8. Using Technology to Support Your Health 9. Wrap Up	1. Build rapport with your Health Coach 2. Identify your core values 3. Set & achieve goals by creating manageable steps 4. Shape your physical & social environment to support your goals 5. Understand & use the healthcare system to support your health 6. Learn to advocate for yourself in healthcare visits 7. Learn about vaccines to protect your health 8. Learn to use technology to access health & social services 9. Review what you have learned!
**Emotional health** *Select 1*	1. Mindfulness & Stress Reduction 2. Mental Health 3. Loss & Grief	Learn to be deliberate in your life by developing positive strategies to manage emotions, stress, anxiety, & grief
**Physical health** *Select 1*	1. Physical Activity 2. Healthy Eating 3. Sleep Hygiene 4. Substance Use	Learn to nurture strong physical health throughout your life by developing healthy habits
**Healthy relationships** *Select 1*	1. Effective Communication & Empathic Listening 2. Conflict Resolution & Compromise 3. Boundaries in Relationships	Learn to build stable & supportive relationships through communication skills, boundary setting, and conflict resolution
**Life skills** *Unlimited selection*	1. Financial Literacy 2. Educational Roadmap 3. Employment Roadmap 4. Parenting Resources	Learn to support your life goals by planning your finances, strengthening your education, and career and using local resources to enhance your family’s wellbeing

Service Navigators will provide participants with resource identification, referrals and linkages, and they may need to provide mentorship with life skills. For example, an uninsured participant may be connected to a public health insurance application navigator in order to obtain health insurance, participants may be assisted in identifying a health care provider that is convenient to their work or home or participants may receive help in scheduling appointments with providers. Table 2 describes the life skills topics addressed in the Service Navigation workbook which will be available in a printed and digital format on the study website.

**Table 2 Tab2:** UCSD RELINK service navigation resources and materials. (Available via a printed workbook and electronically via the study website as a document)

DOMAIN	TOPIC COVERED	DOMAIN	TOPIC COVERED
**Introductory Materials**	• UCSD RELINK CARE Checklist • Using the UCSD RELINK Website • UCSD RELINK Skills for Success Menu	**Health Literacy Handouts**	• Insurance: Understanding & Using Health Insurance • Insurance: Understanding Medicare • Insurance: Medi-Cal • Insurance: Medi-Cal Transportation Benefits • Insurance: Difference Between SSI and Medicare • Healthcare: Doctor Visit Preparation Checklist • Healthcare: Family Medical History • Healthcare: Preventative Care Checklists for Women • Healthcare: Preventative Care Checklists for Men • Healthcare: Vaccine Information and Checklist • Mental Health: Inclusive Mental Health Resources • Mental Health: Constructive Worry Sheet
**Financial Literacy Resources**	• Useful Tips & Resources • Budget Worksheet		
**Digital Literacy Resources**	• Connecting Through Email • Engaging with Social Media • Seeing Providers Through Tele-Health		
**Education Resources**	• Roadmap & Resources		
**Employment Resources**	• Roadmap & Resources • Resume Builder Template • Transportation: MTS Reduced Fares & Passes • Getting a Driver’s License	**Relationship Health Resources**	• Healthy Relationships
		**Substance Use Resources**	• Understanding Fentanyl
**Housing Handouts**	• Apartment Rental Checklist & Resources		
		**Goal Setting Resources**	• Time Management & Goal Setting for Success • Monthly Planner • Weekly Calendar Template
**Legal Support Resources**	• Understanding Your Probation		

### Interventionist credentials & training

For this study, the interventionists will include Health Coaches and Service Navigators. *Health Coaches* will have graduate-level training as licensed therapists (e.g., Marriage & Family Therapist), prior experience serving JIA and deep knowledge about the region. *Service Navigators* will be community members with lived experience or history of serving JIA by providing community resources per participants’ needs (e.g., gender, race/ethnicity, faith, geographic region, income level). Navigators may have university-based education (e.g., Associate of Arts, Bachelor of Arts, Master of Public Health, etc.) in fields adjacent to social services or health professions, but this is not required. Service Navigators will have established relationships with local institutions that explicitly serve the study’s target population.

Health Coaches will undergo standardized training of the intervention, including studying written training manuals, the Health Coaching curriculum workbook, and training videos that describe the intervention philosophy, components and staff roles. Health Coaches will also meet with the principal investigator (PI), project manager, data analyst, and lead mental health faculty advisor to complete the training. The Health Coaches will have prior training in the use of patient-centered, team-based, trauma-informed, and strengths-based care, Mental Health First Aid, de-escalation techniques, SMART Goal Setting, and Case Management (Bath, 2008; Berghuis, 2018; Bjerke & Renger, 2017; Brun & Rapp, 2001; Conzemius & O'Neill, 2009; Epstein & Street, 2011; Gelkopf et al., 2016; Hadlaczky et al., 2014; King, 2017; Levenson & Willis, 2019; Rapp, 1998; Richmond et al., 2012; SAMHSA, 2014a, 2014b; Wallace et al., 2011; Woods et al., 2013). Service Navigators will be trained in the study’s resource directory and key partners and best practices in survey administration and how to administer the online baseline intake survey. Service Navigators and Health Coaches will be trained in documenting services provided, incentives, and adverse events using the study’s case management system. The Health Coach and Navigator will receive ongoing supervision and annual refresher training. Administrative staff (i.e., PI, project manager, data analyst) will meet weekly with the staff to debrief.

All study personnel will also complete university-approved human subjects research protections programs certifications (i.e., Social and Behavioral Research; Biomedical Responsible Conduct of Research) (The CITI Program, 2017) and online trainings focused on effective team-work and remote-work to support participant- and study-staff-facing activities.

### *Study arms & randomization*

After being screened for eligibility, participants will be randomized 1:1 to the treatment or control groups, which are described below and summarized in Table 3. A stratified permuted block randomization will be applied to assess the effect of a health literacy intervention (UCSD RELINK) on recent healthcare use among JIA, comparing a coach-guided treatment group versus a self-study control group. A random permutation method with block sizes 4, 6, and 8 will be used where within each block, half the participants will be randomly assigned to the treatment group and the remaining half will be assigned to the control group. We will use data for biological sex at birth to determine which strata an individual will be assigned to (i.e., male or female) before randomizing the participant to an intervention group. Given the small proportion of female JIA, this approach ensures the treatment and control groups will be balanced within biological sex. The randomization list will be generated using Stata v16 (StataCorp., 2019).

**Table 3 Tab3:** Comparison of the UCSD RELINK intervention delivery by study arm

	**TREATMENT GROUP** **Coach-Guided**	**CONTROL GROUP** **Self-Study**
**Program Orientation**	** + **	** + **
**Health Literacy Intervention Access**		
Curriculum Workbook	** + **	** + **
Study Website	** + **	** + **
**Health Coaching**		
Introduction to Health Coach	** + **	**–**
Weekly Health Literacy Intervention Meetings (~ 45 min; 12 sessions over 6 months)	** + **	**–**
Complete 12 modules (9 Core, 3 Elective)	** + **	** + **
Intervention Delivery Mode	Real-time sessions	Self-Study
Completion Certificates & Final Diploma	** + **	** + **
**Service Navigation**		
Introduction to Service Navigator	** + **	** + **
Weekly Case Management Meetings (30 min; 12 sessions over 6 months)	** + **	**–**
Review of Service Navigation Plan	** + **	** + **
Intervention Delivery Mode	Real-time sessions; Emailed and written referral list	Emailed and written referral list
**Weekly study participation reminders**	** + **	** + **

If this item is provided, it is represented as: “ + ”

If this item not provided, it is represented as: “—”

### Power & sample size

A total of 300 individuals will be enrolled into the study. The power calculation was based on the primary outcome of recent healthcare utilization over the study period (yes/no) and analyzed with a mixed-effects logistic regression. Power was conservatively calculated for recent healthcare utilization at baseline, 6 and 12-months based on the assumption that 60% of the treatment group and 40% of the control group would report recent healthcare use (Ojeda et al., 2021). Accounting for an intraclass correlation coefficient of 0.4 and considering 30% attrition (of the 300 enrolled at baseline), we anticipate we will need 208 participants (104/group) to detect an odds ratio of 1.8 of recent healthcare utilization between the intervention and control group with at least 80% power and 0.05 two-tailed alpha.

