### Study aims & quantitative hypotheses

This study’s primary objective is to assess the effectiveness of a health literacy intervention (i.e., the University of California San Diego Re-Entry Community Linkages [UCSD RELINK] Program) for improving JIA’s healthcare access. Our specific aims for this longitudinal, mixed-methods randomized clinical trial (RCT) are to quantitatively assess the impact of the UCSD RELINK coach-guided health literacy intervention (i.e., health coaching and service navigation) vs. a control group (i.e., self-study of the health coaching program, and brief service navigation support) on healthcare utilization at 6-months and maintenance at 12-months. Secondary quantitative outcomes include assessing health insurance coverage and having a usual source of care. Using qualitative methods, we also seek to understand the impact and maintenance of the intervention at 6 and 12-months.

We hypothesize that participants receiving the coach-guided health literacy intervention will be more likely to report healthcare use at 6 months versus those assigned to the self-study control group. Similarly, we hypothesize that coach-guided health literacy intervention participants will be more likely to report having 1) health insurance and 2) a regular source of care at 6 month follow-up versus control group participants. Maintenance of these outcomes will be assessed quantitatively at 12 months. Additional exploratory outcomes include the types of health services used, type and continuity of health insurance coverage, reasons for being uninsured, delayed care seeking (i.e., has delayed getting medical care in the past 6 months), number of days in hospital, and satisfaction with care.

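### The power paragraph rests on two unreconciled effect sizes (60% vs 40% is an odds ratio of 2.25, not 1.8), and its 80% power for 1.8 does not carry over to the 6-month primary comparison

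*Protocol article*

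**What the plan says.** All the planning figures stand in one paragraph of the protocol article, Power & sample size.

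- Visits: "Power was conservatively calculated for recent healthcare utilization at baseline, 6 and 12-months". The paragraph describes the outcome as use over the study period, analysed by mixed-effects logistic regression.
- Rates: "based on the assumption that 60% of the treatment group and 40% of the control group would report recent healthcare use".
- Result: "we anticipate we will need 208 participants (104/group) to detect an odds ratio of 1.8", "with at least 80% power and 0.05 two-tailed alpha", after an ICC of 0.4 and 30% attrition from 300 enrolled.

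Two other places fix the target differently. In Study aims & quantitative hypotheses, the intervention group "will be more likely to report healthcare use at 6 months versus those assigned to the self-study control group". The Abstract also puts the primary outcomes at 6 months. The section Statistical analyses for survey data goes back to the study period as a whole. It specifies a model with time, treatment and time-by-treatment terms, in which baseline is one of the repeated outcome measurements.

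**The concern.** The paragraph gives two treatment effects and connects the sample size only to the smaller one, while saying that the calculation rests on the larger. A reader cannot tell which effect the trial is designed to detect.

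The target is also unsettled. Power is given for all visits together, including one before treatment starts, while the hypothesis concerns a single visit.

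This paragraph is the only justification for enrolling 300. If the 6-month result is null, a reader will take it that OR 1.8 had at least an 80% chance of being detected. At that time point the chance is close to even.

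**Working it through.** **Inputs from the documents.** Rates 60% and 40%; OR 1.8; 104 per group; ICC 0.4; two-sided alpha 0.05; 80% power; visits at baseline, 6 and 12 months; 30% attrition from 300 (Power & sample size). Allocation 1:1 (Study arms & randomization). Time point 6 months (Abstract; Study aims & quantitative hypotheses).

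**Assumptions made here.** The control rate is 40%. The ICC is the correlation between one participant's yes/no answers at any two visits. The test is the pooled-variance two-proportion test. The arms are equal at baseline, except where a full effect at all three visits is stated.

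**1. The two effect sizes**

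- Stated rates: OR = (0.60/0.40)/(0.40/0.60) = 1.5/0.667 = 2.25.
- OR 1.8 from 40%: odds 0.667 × 1.8 = 1.2, so the treatment rate is 1.2/2.2 = 54.5%.

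**2. Single-visit sample size per group**

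n = [1.960·√(2p̄(1−p̄)) + 0.842·√(p₁(1−p₁)+p₂(1−p₂))]² / (p₁−p₂)²

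- 60% vs 40%: (1.3859 + 0.5831)²/0.04 = 96.9, so 97.
- 54.5% vs 40%: (1.3838 + 0.5879)²/0.02116 = 183.8, so 184.

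**3. Trying to reproduce 104 per group**

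Averaging m visits multiplies n by (1+(m−1)×0.4)/m, which is 0.6 for three visits and 0.7 for two. Adjusting the mean of two follow-ups for baseline gives 0.7 − 0.4² = 0.54.

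| Configuration | n per group | Power at 104 |
|---|---|---|
| 60/40, three visits, full effect at each | 96.9 × 0.6 = 58.2, so 59 | 96% |
| OR 1.8, three visits, full effect at each | 183.8 × 0.6 = 110.3, so 111 | 77.6% |
| OR 1.8, mean of two follow-ups | 183.8 × 0.7 = 128.6, so 129 | 71% |
| OR 1.8, mean of two follow-ups, baseline-adjusted | 183.8 × 0.54 = 99.2, so 100 | 81.8% |

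None returns 104 exactly. The three-visit version reaches 80% at OR 1.83, which rounds to 1.8. The baseline-adjusted version meets the claim of at least 80% with no effect at baseline. The attrition step is sound: 208/0.70 = 297.1, in line with 300.

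**4. Power at 6 months with 104 per group**

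The variance factor is 1 for the visit alone, 1 − 0.4² = 0.84 with baseline as a covariate, and 2(1 − 0.4) = 1.2 for the baseline-to-6-month change (the interaction contrast).

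| 6-month contrast | OR 1.8: power (n needed) | 60/40: power (n needed) |
|---|---|---|
| Direct comparison | 56% (184) | 83% (97) |
| Baseline-adjusted | 63% (155) | 89% (82) |
| Interaction | 48% (221) | 75% (117) |

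The smallest OR detectable at 6 months with 80% power is about 2.19 for the direct comparison and 2.05 baseline-adjusted.

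Simulations for OR 1.8 point the same way. A marginal model (correlation 0.4, 400 runs) gave 46% for the 6-month interaction. A random-intercept logistic model (latent ICC 0.4, 500 runs) gave 40% for the interaction and 57% for a 6-month contrast with a common baseline.

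**5. Could the scale of the OR explain the gap?**

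Suppose the ICC of 0.4 is on the latent logistic scale. The random-intercept variance is then (0.4/0.6) × π²/3 = 2.19, and the approximate ratio of subject-specific to marginal log OR is √(1 + 0.346 × 2.19) = 1.326.

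- If 60/40 are group rates (marginal), the subject-specific OR is exp(0.811 × 1.326) = 2.93, further from 1.8.
- If 60/40 are probabilities for a typical participant, the marginal OR is exp(0.811/1.326) = 1.84 (1.78 by numerical integration), close to 1.8.
- If 1.8 is itself subject-specific, the marginal OR is exp(0.588/1.326) = 1.56, and power is lower than shown in step 4.

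**The case against.** **An expected and a detectable effect can coexist.** Planning for 1.8 while expecting 2.25 would be conservative. The rates themselves may also be the conservative element, since the pilot moved from 36% to 71% with a doctor visit. This stands as a possibility, so it would go too far to call the two figures flatly contradictory. But the text bases the calculation on 60/40 and never presents 1.8 as a smaller, deliberate target.

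**The scale of the OR might link them.** The second reading in step 5 comes close. It requires typical-participant probabilities, whereas the text speaks of percentages of each group, and the paragraph does not mention it. It does not help at 6 months either.

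**The paragraph does not claim 80% power at 6 months.** This is correct. A reader might infer that the 208 is an arithmetic error for the 6-month test. The documents support less: the power is stated for one target and the hypothesis for another, and the sections must be reconciled.

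**Baseline as a visit carrying the effect.** A reader might infer from the list of visits, and from the near match at three visits, that a treatment effect was assumed before treatment. The text does not say so. The baseline-adjusted mean of both follow-ups also uses all three visits, assumes no baseline effect and gives 81.8%. Both readings remain open.

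**The practical harm is limited.** At 60/40, a direct 6-month comparison has about 83% power. This stands, and it is why no larger trial is called for. It does not rescue the stated 80% for OR 1.8, and the interaction contrast falls to about 75% even at 60/40.

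**Conclusion.** The point holds in this form. The stated rates imply OR 2.25, the stated target is OR 1.8, and nothing connects them. Under the stated ICC and three visits the rates would need about 59 per group, not 104.

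At the 6-month time point of the hypothesis, 104 per group gives roughly 48% to 63% power for OR 1.8, depending on the contrast. The 80% figure can be approached only by pooling visits.

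It appears, but is not shown, that baseline may have been credited with a treatment effect. If it was, describing the calculation as conservative is wrong. If the basis was the adjusted mean of both follow-ups, the figure is about right for that contrast but does not address the 6-month hypothesis.

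These figures rest on a 40% control rate, normal approximations and a correlation of 0.4 on the observed scale. A weaker observed correlation would reduce the gain from baseline adjustment and lower the power of the interaction contrast further.

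**What to change.** Rewrite the power paragraph; enrolment stays at 300.

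- State one effect size, and whether the OR is marginal or subject-specific.
- State one time point: 6 months, to match the hypothesis and the Abstract.
- Name one contrast from the mixed-effects model in Statistical analyses for survey data, with baseline as pre-treatment information only.
- Recompute power for that contrast. For 60% vs 40% at 104 per group, the approximate values are 83% (direct), 89% (baseline-adjusted) and 75% (interaction). None should be quoted until the contrast is named, because the first two come from analyses that the section does not specify.
- Remove the claim for OR 1.8. If the averaged follow-up contrast was its basis, label it as the detectable effect for that contrast.
- Describe the calculation as conservative only if the reason is given.

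The cost is one paragraph and one recalculation. The stated detectable effect at 6 months will be less favourable than 1.8.

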### Treatment arm: coach-guided intervention

Participants randomized to the treatment arm will work with their assigned Health Coach and Service Navigator; sessions are scheduled on days/times that are convenient to staff and participants. Participants will engage with the 12-module health literacy curriculum during weekly sessions with their Health Coach, using the curriculum workbook or program website, per their preference, to facilitate learning and exercise completion. Health Coaches will meet with participants during 12 sessions lasting ~ 45 min throughout a 6-month period. The Health Coach will tailor the curriculum per their needs and interests and guide each participant through the reflection exercises. The curriculum is designed for in-person delivery but can also be implemented by video or phone sessions to ensure continuity of the intervention.

Participants will also receive up to 12 sessions of Service Navigation support, per participant preference, lasting 30-min over a 6-month period. At baseline, the Navigator will conduct the intake survey in order to develop the service navigation plan which identifies resources for participants’ most pressing immediate needs. Navigators and Health Coaches will assist with linkage to resources, goal-setting, and mentoring participants through role-playing and modeling of behaviors that support healthcare access and encourage participants to practice new communication and preventive-care skills in real-world settings (e.g., preparing for healthcare visits, self-advocacy). In partnership with the Health Coach and Service Navigator, participants will reflect on barriers and facilitators and develop personalized solutions to support healthcare service utilization. Participants will also receive a written and electronic emailed Service Navigation report including providers’ contact information for independent follow-up.

Importantly, the intervention adopts a team-based approach: the staff support participants through targeted monitoring meetings to support participant self-management, successes, to anticipate new needs, or exchange resources that may impact their shared work. This approach is influenced by the Collaborative Care Model (CCM); for example, CCM has been successfully used with reentrants for care coordination and service linkages across cross-disciplinary teams (Kim et al., 2019).

